#### Predictors collected from patients and family caregivers

Variables (table 3) will be collected in
the validation phase from patients/caregivers using face-to-face/telephone
contacts and postal questionnaires according to their preferences.
IPOS patient version and Distress Thermometer will be collected from
patients at the start of episode, at change of phase of illness and at the end of
episode. Views on Care and Short-Form Health Survey V.2.0 (SF-12v2) will be
collected at the start and end of each episode of care. Selected questions
capturing experiences of integrated care^42^
will be collected at the end of episode only.

**Table 3 T3:** Predictors collected from patients and family caregivers in validation phase
only

Data collection from patients	Data collection from family caregivers
IPOS patient version	Basic demographic information
Distress Thermometer	Distress Thermometer
Views on Care	Two caregiver questions
SF-12v2*	Zarit six items
Patient experiences of integrated care	

*The measure could be completed by a family caregiver if the patient is
too unwell to complete.

SF -12v2, Short-Form Health Survey V.2.0.

All caregiver- reported measures will be collected at the start of episode, at
change of phase of illness and at the end of episode. Where phase length exceeds 4
weeks, data collected from patients (and caregivers) will be captured as a change
of phase. If the patient is transferred to an out-of-scope inpatient setting, we
will follow up with the patient when he or she gets home and
retrospectively collect minimum information about this episode of care.

If the patient is deceased, data such as SF-12v2 and Pall-CSRI will be collected
from the participating caregiver three months after death by postal
questionnaire, along with the bereavement support information and contacts. The
time between death and the postal questionnaire may influence caregivers’
willingness to share their views; shorter periods possibly being too upsetting to
contemplate involvement.^43^ There is mixed
evidence of the best time to make contact with potential participants for
follow-back surveys^44 45^ and 3–4
months post bereavement is considered acceptable by bereaved families.^30^

#### Model of care

Models of care may be a stronger cost driver than patient-level variables.^13 14 16^ Specialist palliative care
services have various configurations of staff, interventions and other
characteristics. Currently, there is no consistent way to define models of
palliative care. A separate, parallel study will be conducted in which
service-level data including the numbers, disciplines and grading of staff, the
nature/duration of their involvement and use of volunteers will be collected to
comprehensively characterise different models of palliative care provision in the
participating sites. With findings from this step, a new categorical variable will
be created representing ‘model of care’ to be included in our
analysis.

### Sample size

In the development phase, based on standard recommendations for fitting multivariate
models, a minimum of 50+8×m (where m is the number of predictors) is required
to test the hypothesis that the population multiple correlation equals zero with a
power of 80%, alpha=5% and a medium effect size for the regression analysis
(R^2^=0.13).^46^ We estimated a
sample size of 450 episodes per setting (allowing for 25% incomplete episodes and up
to 10% of complete episodes being cost outliers with unusually high or low costs). A
total of 1350 patient episodes across settings is needed.

In the validation phase, again a minimum of 50+8×m (where m is the number of
predictors) is required to test the hypothesis that the population multiple
correlation equals zero with a power of 80%, alpha=5% and a medium effect size
for the regression analysis (R^2^=0.13).^46^ In phase II, the number of predictors reflects the casemix variables,
and needs to be clinically relevant^47^ to
ensure a meaningful casemix classification. We expect the final casemix
classification to contain 5–8 casemix variables, based on the Australian
experience.^13^ We have estimated that data
from 114 (50+(8×8)) episodes of care per setting (hospice, hospital,
community) are needed. Assuming an average of three episodes per participant^15^ in this longitudinal phase, this represents at
least 38 participants per setting. Allowing for 50% attrition, we estimate needing a
total of 228 participants, which will provide about 684 patient episodes. The sample
size will be recalculated and inflated using the design effect based on intraclass
correlation which will be estimated through interim analyses. A total of 300
participants across settings is needed, including extra 25% participants allowing for
intraclass correlation.

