### Study design and source of data

This study consists of two phases: development phase (phase I) and validation phase
(phase II). In the analysis part of phase I, we will identify variables that predict
costs to be included in casemix classification through a cohort study with only
clinician data, and develop potential casemix classes for palliative care which will
be tested in individual episodes of care (internal validation). In phase II, we will
prospectively validate these potential classes in a new cohort study with patient,
caregiver and clinician data, and include qualitative interviews to ensure it works
during care transitions and longitudinally over the course of illness (external
validation).

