### Model performance

The performance of the casemix classification will be assessed in both the
development and validation data sets. Classification measures including
sensitivity, specificity, predictive values and net reclassification improvement will
be reported and cut points selected a priori. We will primarily focus on
discrimination for the classification development phase, and assess both
discrimination and calibration for the validation phase.^53^ Discrimination of the classification will be measured using
the concordance statistic and CIs (c-statistic).^54^ Calibration of the classification will be measured using calibration
plot and Hosmer-Lemeshow goodness-of-fit test.^55^

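### The phase II sample size is justified only by power to reject a zero multiple correlation, which gives no assurance for the external validation that phase II is meant to deliver

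*Protocol article*

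**What the plan says.** For phase II the Sample size section states: "In the validation phase, again a minimum of 50+8×m (where m is the number of predictors) is required". The hypothesis is that the population multiple "correlation equals zero with a power of 80%, alpha=5% and a medium effect size", with R²=0.13. The section expects the final "classification to contain 5–8 casemix variables, based on the Australian" experience, takes m=8 and arrives at 114 episodes in each of three settings. At three episodes per participant this is 38 participants per setting. Allowing for 50% attrition gives 228 participants, and an allowance for intraclass correlation gives 300. The size is to be recalculated from an estimated intraclass correlation.

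The purpose of phase II is given elsewhere. Under Study design and source of data: "we will prospectively validate these potential classes in a new cohort study". Under Model performance, the investigators will "assess both discrimination and calibration for the validation phase", using a c-statistic with confidence intervals, a calibration plot and a Hosmer-Lemeshow test. The Abstract adds that the classification will be refined according to how it performs in the validation data.

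**The concern.** The sizing criterion and the purpose of the phase do not match. The overall test with m predictors concerns a model fitted to the phase II data. Rejecting R²=0 shows that the variables predict something about cost in new patients. It does not show that the costs predicted by the phase I classes agree with the costs observed. A classification whose predicted cost differences are far too large would still give a non-zero correlation and pass.

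Nothing in the article connects the 114 episodes per setting, or the 300 participants, to the precision of any discrimination or calibration measure. The stated 80% could therefore be taken as assurance about validation that it does not carry. The setting level matters because the size is built up per setting, and Model specification says the classification will be presented for each outcome across the three settings. Imprecise calibration could also lead to refinement that follows noise.

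**Working it through.** **1. The plan's own figures** (Sample size section)

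- 50 + 8×8 = 114 episodes per setting; 114/3 = 38 participants; 38/(1−0.5) = 76; 76×3 = 228 participants; 228×3 = 684 episodes before attrition. All reproduce.
- Intraclass correlation allowance: 228/(1−0.25) = 304, close to the stated 300; 228×1.25 = 285 is not.
- Power of the overall F test at n=114, m=8, R²=0.13: noncentrality 114×0.13/0.87 = 17.0 on 8 and 105 degrees of freedom, power 82.5%. For 80%, 109 episodes suffice.

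The sizing is correct for the test it names.

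**2. Episodes available at the planned size**

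300 participants over three settings is 100 per setting. 100 × 3 episodes × 0.5 retained = 150 episodes per setting, or 450 pooled.

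Assumed design effect: 1 + (3−1)×ICC with ICC = 0.125 gives 1.25. Effective sizes are 150/1.25 = 120 per setting and 450/1.25 = 360 pooled.

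**3. Precision of a calibration slope**

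Observed cost is regressed on the cost predicted by the unchanged phase I classification, with true slope 1:

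SE = sqrt[(1−R²) / (R²(n−2))], half-width = 1.96 × SE.

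For example, at R²=0.13 and n=120: sqrt[0.87/(0.13×118)] = 0.238, and 1.96×0.238 = 0.47.

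| R² of the classification (0.13 from the plan, others assumed) | Per setting (effective n 120) | Pooled (effective n 360) |
|---|---|---|
| 0.13 | ±0.47 | ±0.27 |
| 0.30 | ±0.28 | ±0.16 |
| 0.50 | ±0.18 | ±0.10 |

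**4. Sensitivity and check, at R²=0.13 per setting**

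- 150 independent episodes: ±0.42.
- ICC 0.5 (design effect 2): ±0.59.
- The bare minimum of 114 independent episodes: SE 0.244, ±0.48. Simulation at n=114 gave a 95% range for the slope of about 0.52 to 1.48 with normal errors and nearly the same with skewed errors, so the formula is adequate here.

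**The case against.** Several points on the other side stand.

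- **Phase II does involve some modelling.** Table 3 lists predictors collected only in the validation phase, Model development enters the variables of Tables 2 and 3 into the models, and the Abstract plans refinement. A regression-based minimum therefore has a role, and it would be wrong to say that the criterion has no place in phase II. It still says nothing about the validation measures, and the phase I classes have to be held unchanged while their performance is measured.
- **R²=0.13 is a planning effect size, not a forecast of performance.** The article gives no expected R² for the classification. The precision must therefore be shown over a range, and it improves markedly at higher R².
- **The planned size is larger than 114 per setting.** The 300 participants include an allowance for clustering, which is why the working uses 150 episodes per setting. The promised recalculation concerns only the design effect and leaves the criterion as it is.
- **The calibration slope is not named in the protocol, and no acceptable width is set.** The slope is used here as a numerical summary of the calibration plot that is named. Calling the result imprecise is a judgement.

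Three stronger readings are tempting and are not supported. A reader might infer that the 80% power is wrong. It is correct for its own hypothesis, and setting it against the power to detect a particular slope compares two different hypotheses. A reader might infer that per-setting calibration is bound to be uninformative, but that depends on R². A reader might also infer that a non-significant Hosmer-Lemeshow test will be taken as successful validation. The article states no such rule, and it pairs the test with a plot.

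**Conclusion.** The point holds as a mismatch between the stated sizing criterion and the stated purpose of phase II, not as an arithmetic error. The 80% power belongs to the test of R²=0 and gives no assurance on discrimination or calibration.

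At the plan's own R², a classification that is truly calibrated within a setting would have a slope interval of roughly 0.53 to 1.47. Such an interval cannot separate good calibration from predicted cost differences that are substantially too large or too small. Pooling, or a classification that explains more of the cost, narrows it considerably.

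These figures rest on three episodes per participant, 50% attrition and R²=0.13 from the plan, and on an assumed design effect of 1.25 and the assumed R² values of 0.30 and 0.50. Whether a statistical analysis plan that is not shown sets a precision target is unknown. The criterion stated in the article would still need the clarification.

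**What to change.** **Sample size section.** State that the 80% power applies to the test of zero multiple correlation and not to the external validation. Add the expected precision of calibration at the planned 300 participants over a range of R², with the design effect assumption, as in the table above.

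**Model performance section.** Report the calibration slope and intercept of the unchanged phase I classification with participant-clustered 95% confidence intervals, per setting and pooled, before any refinement. Base the calibration conclusion on these intervals. State that a non-significant Hosmer-Lemeshow test will not be taken as evidence of good fit.

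A pooled primary result is not required. It would change the per-setting basis of the plan and is a trade-off for the investigators.

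**Cost.** Wording in two sections and a minor additional analysis, with no more participants. The downside is a less favourable stated assurance and softer claims for individual settings.

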### Missing data and data handling

Data will be collected prospectively and recorded on an electronic database. Any data
transferred from the sites to the central study database will be carried out under
the NHS Code of Practice on Confidentiality. Data will be cleaned and cross-checked
using a number of internal checks (automated data validation on entry, independent
cross-checking of a 5% sample of data from each site and range checking across all
data types) to track errors and inconsistencies and amend where possible. Checked
data will be transferred to statistical software (Stata SE V.12) for analysis.
Missing value analysis will be used to quantify missing values and understand the
reason for missing data: dropout of participants, errors in data entry and missing
with no identifiable reasons. We will adopt multiple imputation technique based on
Markov Chain Monte Carlo techniques if the percentage of observed missing values in
independent variables exceeds 10% provided values are missing at random, and carry
out sensitivity analysis for effects on casemix classification, predictive validity
and misclassification, where feasible.

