#### Predictors collected from clinicians

In both the development and validation phases, clinicians will record demographic,
clinical and episode start administrative data. Episode end data will be collected
at the end of each episode of care. Casemix data include phase of illness (stable,
unstable, deteriorating, dying), functional status (measured by Australia-modified
Karnofsky Performance Status (AKPS)), dependency (Modified Barthel Index), problem
severity (Integrated Palliative care Outcome Scale—IPOS staff version) and
caregiver needs (table 2). The measures are
available directly from phase of illness (www.pcoc.org.au), AKPS,^40^ Modified Barthel Index^41^ and IPOS (www.pos-pal.org), respectively. Phase of illness will be assessed
daily for people receiving inpatient care and at each face-to-face contact basis
for those receiving community-based care. Other variables including AKPS, Modified
Barthel Index, IPOS staff (and caregiver needs when feasible) will be collected at
the start of episode, end of episode and at change of phase of illness.

**Table 2 T2:** Data from clinicians in both development phase and validation phase

Type of data	Proposed cost predictors
Demographic data	Age
	Gender
	Postcode
	Ethnicity
	Marital status
	Living circumstances
	Need for interpreter
	Setting of care
Clinical data	Primary diagnosis
	Secondary diagnoses
	Comorbidities
Episode start and end data	Episode start date
	Episode end date
	Endpoint of episode (discharged or died).
	Discharge destination, if discharged
Key casemix	Phase of illness at start of episode
	Functional status (AKPS)
	Dependency (Modified Barthel Index)
	Problem severity (IPOS staff version)
	Family/caregiver needs

AKPS, Australia-modified Karnofsky Performance Status; IPOS, Integrated
Palliative care Outcome Scale.

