### Model development

The distribution of casemix criteria (cost predictors) in the participant population
will be described based on phase of illness, functional status and problem severity,
using parametric or non-parametric statistics, as appropriate. In order to reduce the
number of cost predictors, we will initially use univariate analysis to explore the
association and strength of association between casemix criteria and cost of the
episode of care (quantifying cost by per diem cost, per phase cost and total cost of
episode). We will use generalised linear model (multivariate regression model) to
select variables that will then be applied in a hierarchical manner to form a
branching classification in which each cost driver is incorporated only once.

We will select variables according to how much of the predictive error
(R^2^) each variable predicts and the related P value. After each
bootstrap iteration, we will rank the variables according to these two criteria and
remove the weakest (non-significant) predictor. Variables shown in tables 2 and 3 and the newly created
categorical variable representing ‘model of care’ will be initially
entered into the models and then non-significant predictors removed at each iteration
using a Bootstrap subsampling strategy. We will create dummy variables to enable each
level of phase of illness and model of care (categorical variables) to be assessed
individually. Internal validation will be conducted by using such methods as
bootstrapping or cross-validation to quantify any optimism in the predictive
performance (calibration and discrimination) of the developed classification.

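### A 10% trigger for multiple imputation, conditional on missing at random, ignores how gaps accumulate over 20 jointly entered predictors and leaves lower missingness without a stated method

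*Protocol article*

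**What the plan says.** Under Missing data and data handling, the protocol article writes "We will adopt multiple imputation technique based on" Markov chain Monte Carlo. This applies only if the percentage missing in the "independent variables exceeds 10% provided values are missing at random". No method is given for missingness at or below 10%, or for values judged not to be missing at random. The article does not say whether the 10% is counted per variable, over all predictor values pooled, or per episode. A missing value analysis will look into the reasons for gaps. The authors also plan to carry "out sensitivity analysis for effects on casemix classification, predictive validity" and misclassification, but only where feasible.

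Under Model development, "Variables shown in tables 2 and 3 and the newly created" model-of-care variable go into the models at the start. Variables are then ranked by R-squared and P value, and the weakest is removed at each bootstrap iteration. Table 2 ("Data from clinicians in both development phase and validation phase") lists 20 variables. Table 3 ("Predictors collected from patients and family caregivers in validation phase" only) adds nine in phase II.

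Among the key casemix measures, "Barthel Index, IPOS staff (and caregiver needs when feasible) will be collected at" episode start, episode end and change of phase, so gaps are foreseen for at least one of them.

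Under Sample size, the development phase has a "sample size of 450 episodes per setting (allowing for 25% incomplete episodes and up" to a tenth of the complete ones as cost outliers.

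**The concern.** A percentage trigger looks at the rate of missing values, whereas a regression without imputation loses whole episodes. With many predictors entered together, a low rate in each can leave few episodes with every predictor observed. The rule could therefore withhold imputation in data where the episode loss is already large.

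The second condition has its own problem. Observed data can show which recorded characteristics go with missingness, but cannot establish that values are missing at random. Read literally, data judged not missing at random would stay unimputed even above 10%, where the loss of episodes is greatest.

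Stepwise removal adds to this. If each model used its own complete cases, dropping a variable with gaps would bring episodes back. Successive R-squared and P values could then come from different sets of episodes, and the ranking that decides which variables enter the classification would partly reflect that.

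At stake are the precision and stability of variable selection in phase I and, if gaps are related to condition or cost, how representative the resulting classes are.

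**Working it through.** **Inputs.** From the article: 20 variables (Table 2: 8 demographic, 3 clinical, 4 episode, 5 key casemix), or 21 with model of care; 450 development episodes per setting; allowances of 25% incomplete and up to 10% cost outliers; the rule 50+8m. The article gives no missingness rates, so the per-variable rate q and the correlation between gaps are assumptions, shown as ranges.

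**The plan's own figures.** 3 × 450 = 1350, and in the validation phase 50 + 8 × 8 = 114; both agree with the article. The development m is not stated. For the 20 variables of Table 2 the rule gives 50 + 8 × 20 = 210 episodes per setting.

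**Base.** If the 25% allowance is meant to cover missing predictors, it must not be deducted before the complete-case share is applied. Removing only the outliers leaves 450 × 0.90 = 405.

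**Independent gaps.** Share complete = (1 − q)^20.

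| q per variable | Share complete | Of 405 |
|---|---|---|
| 2% | 0.98^20 = 66.8% | about 270 |
| 5% | 0.95^20 = 35.8% | about 145 |
| 9% | 0.91^20 = 15.2% | about 61 |

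**Thresholds under independence.**
- The 25% allowance is used up at q = 1 − 0.75^(1/20) = 1.4%.
- Half of all episodes are lost at q = 1 − 0.5^(1/20) = 3.4%.
- The rule fails when 405 × (1 − q)^20 < 210, that is, above q = 1 − (210/405)^(1/20) = 3.2%.

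**Less severe assumptions.** For correlated gaps, missingness in each variable is taken as a latent normal variable falling below the cut-off t = Φ⁻¹(q), with common correlation ρ. The share complete is then the integral over u of φ(u) × [1 − Φ((t − √ρ·u)/√(1 − ρ))]^20.

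| Assumption | 5% per variable | Of 405 | Near 10% per variable | Of 405 |
|---|---|---|---|---|
| 20 variables, independent | 35.8% | 145 | 12.2% | 49 |
| Only 12 variables with gaps, independent | 0.95^12 = 54.0% | 219 | 0.90^12 = 28.2% | 114 |
| 20 variables, ρ = 0.5 | 66.1% | 268 | 48.4% | 196 |
| 20 variables, ρ = 0.9 | 86.3% | 350 | 76.4% | 309 |

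If the 10% is counted as episodes with any gap, the loss below the trigger is at most 10%, so at least 405 × 0.90 = 364.5 episodes remain.

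**The case against.** The strongest reply is that complete-case analysis is nowhere written. The article says when imputation is used, is silent otherwise, and may leave the rest to an analysis plan that is not shown. That is right as far as it goes: complete-case regression at or below 10% is an inference. Nor does the article say whether the analysed episodes are held fixed during variable removal. The trigger and the missing-at-random condition, however, are stated rules and can be judged as they stand.

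A reader might infer that the plan will discard most episodes. The documents do not support that. The meaning of 10% is open, and on the per-episode reading the loss is small. Age, gender, setting and episode dates should be nearly complete, and data are validated on entry. Model development also begins with univariate analysis to reduce the number of predictors, although it then says that all listed variables are initially entered. Correlated gaps at 5% leave a clear majority of episodes.

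A reader might also infer that the sample-size requirement is broken outright. It is not: at 2% per variable about 270 episodes remain against 210, and at 5% the rule is still met with 12 variables or with correlated gaps. Starting from 450 × 0.75 × 0.90 = 304 would make the figures worse (203, 109 and 46 at 2%, 5% and 9%), but may remove incomplete episodes twice.

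Finally, it is plausible that gaps concentrate in very ill or short-stay patients, but the article does not say so. If they did, the gaps would be clustered and fewer episodes would be lost than under independence. The planned sensitivity analysis is a partial safeguard, weakened by being done only where feasible.

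**Conclusion.** The point holds in a conditional form. On a per-variable or pooled reading, the trigger ignores accumulation over jointly entered predictors, and a rate well below 10% can cost far more episodes than the 25% allowed for. At 5% per variable the complete share runs from 36% (20 variables, independent gaps) to 86% (latent correlation 0.9). The 50+8m rule with m = 20 fails above about 3.2% per variable, given independence and a base of 405.

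These results assume complete-case analysis at or below the trigger, which is the natural reading but is not stated, and missingness rates that the article does not give. Making imputation depend on missing at random is unsound on any reading, because the data cannot establish it. Shifting sets of episodes during variable removal are a possibility, not a stated feature of the plan.

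**What to change.** - Remove the 10% trigger, and impute whenever any candidate predictor has missing values. Include cost, setting, site and endpoint of the episode in the imputation model.
- Treat inapplicable items, such as discharge destination after death, as not applicable and do not impute them.
- Keep missing at random, but as a stated working assumption and not as a precondition. Add a sensitivity analysis for departures from it. Deleting the assumption altogether would not help, since standard multiple imputation relies on it.
- Run variable selection on one fixed set of episodes, so that R-squared and P values are comparable between steps.
- Report the complete-case analysis as a sensitivity analysis.

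The cost is a change of wording and extra computing to combine imputation with the bootstrap. No new data are needed.
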